## Subject inclusion criteria:

Healthy children aged 6-11 months, 5-6 years or 10-11-years, who reside within a relatively short and easily accessible distance (<30 km) to the study sites, and do not plan to travel away during entire the study period (~2 months).

## Subject exclusion criteria:

Children with known thrombocytopenia or bleeding disorders; children acutely ill or with signs of acute infection (e.g. fever ≥ 101 F) at the time of enrolment; residence >30 km from study site; or families expecting to be absent during the 60-day study period. A diagnosis or suspicion of immunodeficiency disorder (either in the participant or in a member of the immediate family) will also render the child ineligible for the study.

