## Description and justification for the route of administration, dosage, dosage regimen, and treatment period:

At study entry (day 0), subjects will be randomized to one of three study arms. Arm A will be vaccinated with one dose of bOPV administered by the oral route at day 0; arm B will receive one dose of IPV intramuscularly; and arm C will not receive any vaccination. At day 28, all subjects will receive a single dose of bOPV that serves as a challenge dose.

A study from India [18] and a review of mOPV clinical studies is available [19].

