# Trial Design

Local community mobilization coordinators (CMCs) working with the Global Polio Eradication Initiative (GPEI) will identify families with children in the target age-group (i.e. 6-11 months, 5-6-years, and 10-11-years). Surveillance Medical Officers (SMOs) will visit households of potential candidate families, explain the study to the parents or guardians, and facilitate transportation to one of the study sites for those interested to participate. Approximately 10 study sites will be chosen in areas identified as high-risk for poliovirus transmission.

At the study site, a physician will conduct a short interview and physical examination. After obtaining informed consent from the parents (and assent from children of age 10-11 years), the study participant will be assigned a study number and allocated to a study arm. For this, the parent or child will select a closed envelope that includes the study arm from a basket. Then a baseline blood sample collected by venipuncture, oral (crevicular) fluid, and stool samples will be collected before vaccine administration.

Note: crevicular fluid will not be collected in the 6-11 month age group because of the absence of teeth.

In a subset of children 10-11 years of age (~175-200 children) a second blood sample will be collected at 7 days by venipuncture for the ELISPOT test.

In all children, at 28 days, another blood sample by venipuncture, another oral (crevicular) fluid sample and a stool sample will be collected before the subjects receives the challenge vaccine (bOPV). Thereafter, at days 3, 7 and 14 stool samples will be collected. And finally, at day 56, another serum sample and oral fluid sample will be collected. At this time, having fulfilled the study requirements, the children will exit the study.

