## The identification of any data to be recorded directly on the CRFs (i.e. no prior written or electronic record of data), and to be considered to be the source data:

A questionnaire (Annex IV) will serve as the primary data collection instrument, and will serve as the source data.

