# Quality Control and Quality Assurance Procedures

### Study Monitoring and Source Data Verification

After appropriate ethical approval by an Institutional Review Board (IRB) is available (and the final protocol has been amended as required by IRB), the field study clinics will be set up to ensure the presence of all logistics. All study staff will be given detailed training on the study and their specific role. During the set-up of study sites and trainings, the requirements of GCP, protocol procedures, and all logistical issues will be discussed at length. The subjects cannot be enrolled until occurrence of these processes and their documentation.

After the study is initiated, the study monitor will be in regular contact with the sites to obtain information on the performance of the study. These contacts will be scheduled to take place at regular intervals. Subsequent to start of recruitment, routine monitoring visits would occur (approximately every 4 weeks) after prior appointment with the investigators.

The investigator and his/her staff are obliged to devote a suitable amount of time and an appropriate place for the monitoring visits. During each visit, the monitor will review the Case Report Form (CRF) of each subject in the study with regard to completeness, thoroughness and compliance with the protocol. In addition, at a minimum, the original subject data (e.g., entry cards, index cards, original findings) will be reviewed to ensure that:

- subject informed consent is incorporated;
- inclusion/exclusion criteria are properly followed;
- the CRF data are consistent with the questionnaires, the source data;
- all relevant clinical and laboratory findings and concomitant medication are documented in the CRFs;
- quantity and dosing schedule of concomitant medication is documented in the CRFs;
- quantity and dosing schedule of the Investigational/Comparator Product is in accordance with the protocol;
- all relevant information (e.g., any adverse event) has been recorded in the appropriate place in the CRFs;
- the Investigational/Comparator Product is being stored correctly, and its supply is being properly accounted for;
- Incorrect or illegible entries in the CRFs would be submitted to the investigator for correction.

The monitor will retrieve completed CRFs during the regularly held monitoring visits.

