# Village Block: CMC area

**Eligibility criteria**

- Child’s residence < 30 km from study site Yes / No
- Child’s age: 6-11 months, 61- 72 months or 120 – 131 months? Yes / No
- Child and family planning to travel / move in the next 2 months? Yes / No
- Diagnosis or suspicion of immunodeficiency in the child or family member? Yes / No
- Child has known coagulation disorders that contraindicate venipuncture? Yes / No
- Child has history of severe allergic reaction to a medication or to OPV? Yes / No
- Has the child had diarrhea in the last 1-2 days (3 or more liquid stools per day)? Yes / No
- Does the child have any acute infection or other acute condition now? Yes / No

If yes, specify _____________________________________

Temp: _________

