**Based upon the above criteria is this child a candidate for the study? Yes / No**

***If child has any of the previous criteria that contraindicates participation, STOP THE QUESTIONNAIRE;*** *provide medical advice and oral medication if required, and say farewell.*

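### The household enrolment form screens for bleeding risk more narrowly than the protocol's exclusion criterion (low-severity inconsistency)

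*Protocol*

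**What the plan says.** Under Subject exclusion criteria, the Protocol opens its list with "Children with known thrombocytopenia or bleeding disorders; children acutely ill or with signs of acute infection". The bleeding part carries no qualifier of severity or procedure, and it lists thrombocytopenia separately from bleeding disorders.

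The enrolment questionnaire in Annex V has one item on the subject: "Child has known coagulation disorders that contraindicate venipuncture? Yes / No". After the list of items it asks "Based upon the above criteria is this child a candidate for the study? Yes / No". If the answer is yes and the parents accept, the form ends with arranging transport to the study site. It is therefore completed before the child arrives there. This fits the Trial Design section, in which medical officers visit households first.

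At the site, the Trial Design section says: "At the study site, a physician will conduct a short interview and physical examination". Consent, allocation by drawn envelope, baseline samples and vaccination follow, in that order. On treatment, "arm B will receive one dose of IPV intramuscularly".

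On the status of the form, the Protocol says that a questionnaire "will serve as the primary data collection instrument, and will serve as the source data". That sentence cites Annex IV, but the list of supplements puts the case record form at Annex V, and the only questionnaires shown are there.

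**The concern.** Two texts in the same document set different tests for the same exclusion, and the one used in the field is the narrower. A child with known thrombocytopenia, or with a mild bleeding disorder judged compatible with a blood draw, is ineligible under the criterion but can truthfully be recorded as "No" on the form and marked a candidate.

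Two things are at stake, both modest. One is safety: such a child would have blood drawn and, if allocated to arm B, would receive an intramuscular injection, which the form item does not mention. The other is the eligibility record: because the questionnaire is the source data and never puts the protocol's question, it need not show that the criterion was checked, and a monitor comparing records with it may find nothing to query.

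**Working it through.** This is mainly a comparison of texts, with one line of arithmetic.

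**1. The two tests side by side**

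| Feature | Exclusion criterion | Annex V enrolment form |
| --- | --- | --- |
| Thrombocytopenia | Named | Not named |
| Other bleeding conditions | Any known bleeding disorder | Known coagulation disorders |
| Qualifier | None | Tied to venipuncture |
| Intramuscular injection | Covered, since there is no qualifier | Not mentioned |

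**2. Does the result depend on how the qualifier is read?** There are two readings of the form item.

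- *Restrictive:* only disorders that rule out a blood draw count. Mild disorders then pass the form but fail the criterion.
- *Explanatory:* the clause merely says why the question is asked. Coagulation disorders of any severity are then caught, but thrombocytopenia, a platelet disorder, is still not named.

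The form is narrower than the criterion on either reading, and more so on the first.

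**3. Does a later form close the gap?** The Day 0 page records consent, demographic data, height, weight, temperature, sample collection and vaccine administration. It has no bleeding item. The day 7, 28 and 56 pages ask about health since the last visit, again without one. On the enrolment form itself, the item on acute infection or another acute condition might catch an acute bleeding problem but not a stable, known one. The consent and information sheets (Annexes III and IV) were not in the text reviewed, so nothing is claimed about them.

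**4. Share of children given the intramuscular dose** (Annex I, item 7: 110 per age group and arm)

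- Total: 110 × 3 age groups × 3 arms = 990, which reproduces the planned enrolment.
- Arm B: 110 × 3 = 330.
- Share: 330 / 990 = 1/3.

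A child wrongly passed by the form and then enrolled therefore has about a 1 in 3 chance of the injection. This uses the planned equal numbers; drawing envelopes from a basket could leave the actual share slightly different.

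**5. Number of children affected.** This would be 990 × (prevalence of known disorders missed by the form item) × (probability that the site checks also miss them), with one third of the result in arm B. The documents give neither of the two probabilities, so no count is offered.

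**6. Effect on the analysis.** The form is completed before allocation, so it cannot create a difference between arms in who is admitted. The primary comparison, power and analysis set do not depend on it.

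**The case against.** The strongest reply is that the form is only a household pre-screen and that the exclusion criterion governs. A yes on the form sends the child to the site; it does not enrol the child. A physician then interviews and examines each child before allocation. The inclusion criterion asks for "Healthy children aged 6-11 months, 5-6 years or 10-11-years". The study must be run in compliance with the protocol, monitors are to check that the eligibility criteria were followed, and "All study staff will be given detailed training on the study and their specific role". In addition, every child has blood drawn on day 0 before any vaccine is given, so a question about fitness for venipuncture prompts some thought about bleeding in every arm.

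Most of this stands, and it is why the point is minor. What it does not do is make the two texts agree. The site interview is described as short, and no bleeding question is specified for it. A known disorder comes to light through history, so someone has to ask. Monitoring visits fall about every four weeks, too late to prevent a day-0 injection.

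A reader might infer more: that the form overrides the criterion, that excluded children will be injected, or that some disorders are acceptable for a blood draw yet unsafe for an intramuscular injection. The documents support none of these. They nowhere give the form precedence, they give no prevalence, and they do not compare the bleeding risk of the two procedures. The form also carries items that the exclusion list does not name, such as severe allergy. That is a separate mismatch in the opposite direction, with the form the stricter text, and it adds nothing here.

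**Conclusion.** The inconsistency is real and of low severity. As written, the form can pass a child whom the protocol excludes, and no later form shown asks the missing question before the blood draw or, for the planned 330 of 990 children in arm B, before the intramuscular dose. The wording difference is certain. Actual harm is not shown, and the site safeguards make it unlikely. No number of affected children can be given. The statistical conclusions of the trial are untouched.

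The conclusion rests on the forms shown being the complete set of screening forms, and on the planned equal allocation for the one-third share.

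**What to change.** Before enrolment starts, reword the Annex V item to: *Child has known thrombocytopenia or bleeding disorder? Yes / No*. This uses the criterion's own terms, drops the reference to venipuncture, and puts the answer in the source data. The exclusion criterion needs no change.

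The cost is one line on one form. The downside is at most a few more screen failures, all in children the protocol already excludes.

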## Subject withdrawal criteria (terminating investigational product treatment/trial treatment) and procedures specifying 1) when and how to withdraw subjects; 2) the type and timing of the data to be collected for withdrawn subjects; 3) whether and how subjects are to be replaced; 4) the follow-up for subjects withdrawn from investigational product treatment/trial treatment:

As mentioned above, subjects may withdraw from the study at any point. The data collected for withdrawn subjects, in addition to standard questionnaire data, will include the reason for withdrawal. Subjects will not be replaced. No additional follow-up is envisioned for withdrawn subjects. If children miss a scheduled blood sample collection, they will be excluded from final analysis. Children missing a stool or gingival fluid sample but having other samples available will be included in the study. If children develop an acute illness during the study, medical treatment will be provided as explained on page 20, and sample collection will continue as scheduled, unless the illness is associated with a contraindication for venepuncture or the parents refuse sample collection. In this case, the study subject will be withdrawn from the study as explained above.

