# Trial Objectives and Purpose

## Mucosal immunity:

- To compare baseline mucosal immunity (through different methods) among three age groups with several degrees of protection acquired through immunization:
  - Infants 6-11 months of age will have received a few OPV doses
  - Children 5-6 years of age will have received multiple OPV doses in campaigns and are expected to have the highest levels of mucosal and humoral immunity
  - Children 10-11 years of age will not have received booster OPV doses for > 5 years. They are expected to have high antibody titers but may have waned mucosal immunity.
- To determine whether one dose of bOPV or IPV significantly reduces excretion of poliovirus types 1 and 3, respectively, following a challenge dose with bOPV, compared to an unvaccinated control arm.
- To determine whether one dose of bOPV or IPV significantly increases sIgA in crevicular fluids and stool samples, and to examine whether the increase in specific SIgA in these specimens is correlated to a reduction in excretion of Sabin poliovirus types 1 and 3 following the challenge with bOPV. This will allow evaluating the use of sIgA as a surrogate test for assessment of mucosal immunity.
- To determine the robustness of the mucosal immune response by study arm and age group, by measuring poliovirus antibody-secreting cells in an ELISPOT-spot assay 7 days after the administration of the study vaccine.

Humoral immunity:

- To determine whether one dose of bOPV or IPV will significantly increase seroprevalence and booster antibody titers compared to unvaccinated children.
- To assess whether one dose of IPV will significantly increase seroprevalence and antibody titers compared to a single dose of bOPV.
- To examine the correlations between antibody titers in blood and shedding of poliovirus after a challenge dose, for each vaccine study arm and age group.
- To examine the correlation between levels of IgA in serum and levels of secretory IgA in crevicular fluids and stool samples, before and after the booster vaccine dose, to gain further understanding on the mechanisms of mucosal immunity against poliovirus.
- To analyze correlations between levels of secretory IgA in crevicular fluids and stools and the ELISPOT test results, to better understand mucosal immunity against poliovirus.

Safety:

- To assess adverse events following vaccine administration.

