## The selection of subjects to be included in the analysis (e.g., all randomized subjects, all doses subjects, all eligible subjects, evaluable subjects):

As stated above, only subjects who complete all study requirements including all study visits and provide sufficient quantities of sera samples for analysis will be included in the analysis.

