# Description of the event

# Date when event started (dd / mm/yy): ____ / ____ / _____ Time (hh:mm): _____ : _____

# Describe symptoms and signs:

#

#

#

Actions taken:Medical advice Referral to health facility Referral to Hospital

If referred to health facility or Hospital, specify name:

Medications given:

Diagnostics tests performed:

Date when event resolved (dd / mm/yy): ____ / ____ / _____

Final diagnosis:

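### A child withdrawn because of illness gets no further follow-up and falls outside the only stated analysis set, with no exception for the safety objective

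*Protocol*

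**What the plan says.** Four parts of the protocol bear on this.

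- **Subject withdrawal criteria.** Sampling continues through an acute illness "unless the illness is associated with a contraindication for venepuncture or the parents refuse sample collection". For those exceptions the rule is: "In this case, the study subject will be withdrawn from the study as explained above". On what happens next: "No additional follow-up is envisioned for withdrawn subjects". The section also says "If children miss a scheduled blood sample collection, they will be excluded from final analysis". On retained data it says "The data collected for withdrawn subjects, in addition to standard questionnaire data, will include the reason for withdrawal".
- **Statistics, selection of subjects for the analysis.** The analysis takes in "only subjects who complete all study requirements including all study visits and provide sufficient quantities of sera samples for analysis". The section on missing, unused and spurious data gives the same definition of an evaluable child, under the label of a modified intention-to-treat analysis. Its only relaxation is for a missing stool or gingival fluid sample.
- **Trial Objectives, Safety.** The objective is "To assess adverse events following vaccine administration".
- **Statistics, statistical methods.** This section names Annex II as the statistical analysis plan. Annex II covers excretion and antibody titres and contains no safety analysis.

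**The concern.** The withdrawal rule ties safety follow-up to the ability or willingness to give blood. An illness after vaccination can end a child's participation, and the illness may itself be the adverse event that the safety objective is meant to count. The completer rule then applies to the analysis as a whole. Followed as written, the safety summary describes children who were well enough, and whose families were willing, to finish. Loss of this kind may depend on the outcome, and a larger trial would not remove it.

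The stake is completeness of the safety account. The protocol names vaccine-associated paralytic poliomyelitis and anaphylaxis as the serious risks and says the exact risk of the former after bOPV is unknown. With events this rare, one case left out or left without an outcome alters the safety statement.

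**Working it through.** **1. When the protocol looks for adverse events** (Annex V forms; Assessment of Safety)

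| Time | What is scheduled |
| --- | --- |
| Day 0 | 30 minutes' observation after vaccination |
| Day 7 | Health enquiry, only in the subset sampled for ELISPOT |
| Day 28 | Health enquiry, then the bOPV challenge for all arms with a 15-minute check |
| Days 31, 35, 42 | Stool collection only; no health question on the form |
| Day 56 | Health enquiry |

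Between visits the system is passive: parents are told to contact study staff, and the serious-illness instruction is framed for the time the child is enrolled. After the 15-minute check at challenge, day 56 is thus the only scheduled enquiry. A child withdrawn for illness between days 28 and 56 does not reach it. The section on follow-up after adverse events promises referral and care but gives no duration of follow-up.

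**2. Who is in the analysis**

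A child is in the set only if all visits are completed and sera suffice. A child who dies before day 56 cannot meet this. A child withdrawn for illness before day 56 cannot meet it either. No sentence exempts the safety summary.

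**3. The plan's own numbers**

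Inputs from the sample size section and Annex I: 89 completers and 110 enrolled per arm and age group, 3 arms, 3 age groups, 15–20% drop-out.

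- Completers: 9 × 89 = 801, as stated.
- Enrolled: 9 × 110 = 990, as stated.
- Outside the set at 801 completers: 990 − 801 = 189, and 189 / 990 = 19.1%, inside the stated drop-out range.
- The stated range itself: 0.15 × 990 = 148.5 to 0.20 × 990 = 198.

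These counts cover drop-out for every reason. The documents give no rate of illness-related withdrawal.

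**4. How far a safety rate could move** (assumed rates; the documents give none)

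Let *r* be the true proportion of the 990 with a serious event and *f* the share of those children outside the set. The rate seen in completers is 990 × *r* × (1 − *f*) / 801.

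| *r* | *f* = 25% | *f* = 50% | *f* = 75% |
| --- | --- | --- | --- |
| 0.5% | 0.46% | 0.31% | 0.15% |
| 1% | 0.93% | 0.62% | 0.31% |
| 2% | 1.85% | 1.24% | 0.62% |

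Example: 990 × 0.01 × 0.5 / 801 = 4.95 / 801 = 0.62%. If loss were unrelated to events, *f* would be 189 / 990 = 19.1% and the observed rate would equal *r*. Bias arises only when children with events are lost more often than that. For deaths before day 56, *f* is 100%.

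**5. Precision**

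With no events in an arm, the one-sided 95% upper bound is 1 − 0.05^(1/n). For all 330 enrolled per arm it is 0.90%; for 267 completers per arm (3 × 89) it is 1.12%. This cost is small; the selection in step 4 matters more.

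**The case against.** The strongest reply is that serious events leave the trial by a route that does not depend on finishing it. They go to the sponsor within 24 hours and to regulators and ethics committees within 15 days, under data and safety monitoring board oversight. The adverse event form sends paralysis, anaphylaxis, hospitalization and death to the coordinator and the AEFI committee. Questionnaire data and the reason for withdrawal are kept. This stands: a reader might infer that serious reactions vanish from the trial, and the text does not support that. What is lost is their place in the analysed results, and observation after withdrawal.

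A second reply is that the completer rule reads as an immunogenicity set, since its criterion is sera, and that a safety population is commonly left to a separate analysis plan. It is plausible that this was the intent. But the protocol fixes the set itself without limiting it to immunogenicity, and names Annex II, which has no safety analysis, as its plan.

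Other stronger readings are tempting and should be set aside.

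- A reader might take any seriously ill child to be withdrawn. The default is that sampling continues, and the only contraindications to venepuncture that the documents point to are bleeding or coagulation disorders. That withdrawn children are those likeliest to have had a serious reaction is inference.
- A reader might see a contradiction with the adverse event form, which asks for a resolution date, final diagnosis and causality. The AEFI judgement does not need continued enrolment and allows an unclassifiable verdict, and events resolved before withdrawal can be completed. Only events still open at withdrawal are left unclear.
- A reader might conclude that harm is understated in the vaccinated arms. The rule is the same in all arms, all receive bOPV at day 28, and nothing shows differential loss.
- On the protocol's figure for trivalent vaccine, about 1 case per million doses, 330 + 990 = 1,320 bOPV doses give an expected 0.001 paralytic cases. The concern is the completeness of the safety account, not an expected cluster of such cases.

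**Conclusion.** The point holds and should be fixed. As written, a child who dies, or who is withdrawn for illness before day 56, is outside the analysed safety results, and events arising or still open after withdrawal may not be captured. At the planned minimum of 801 completers, 189 of 990 children (19.1%) are outside the only stated set. That is a ceiling from all-cause drop-out. The size of any bias cannot be estimated from the documents; the table of rates rests wholly on assumed values.

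The matter falls short of a must-fix. Safety is an objective but neither a primary nor a secondary endpoint, both vaccines are licensed, serious events have their own reporting route, and the primary excretion comparison does not depend on the safety set.

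**What to change.** 1. In the two Statistics sections that define who is analysed, restrict the completer rule to the immunogenicity and excretion analyses. State that safety is summarised for all enrolled children by vaccine received (including none), regardless of samples given or visits completed.
2. In the withdrawal section, separate stopping sample collection from leaving the study. A child who stops sampling because of illness or parental refusal stays in adverse event data collection to day 56, and events open at that point are recorded to outcome, unless consent for contact is withdrawn.
3. Reconcile the withdrawal section with the section on follow-up after adverse events and with the resolution, diagnosis and causality fields of the adverse event form, so that it is clear who completes them for a withdrawn child.

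The cost is a few sentences and some extra contacts by staff already working in the area. Some of those contacts will be incomplete. Sample size, treatment and the primary analysis do not change.
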